### Sample size and power calculation

Power based on the primary outcome “adherence score” was calculated for the sample size of 400 consenting parents in each group. Assuming that the difference in the log odds of the groups will be 0.3, 0.4 or 0.5 (maximum score 4), this corresponds to odds ratios of 1.35, 1.5 and 1.65, respectively. The power was simulated with 5000 replications and found to be 0.44, 0.66, and 0.86 for the three different scenarios. Power for the primary outcome “responsiveness score” was calculated for the same sample size as above, using the mean differences of 0.8, 1.6 and 3.2 (maximum score 20). The standard deviation was assumed to be 4, 8 and 16 for each option. With an SD of 8, the power for the three scenarios is 0.29, 0.81 and 0.99 respectively for this outcome.

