**Methods:**

IMPROVE is a cluster-randomized controlled trial with two arms to evaluate and compare the effects of two different bundles of implementation strategies on intervention fidelity expressed as adherence and responsiveness at 12 and 24 months (primary outcomes). Thirty schools in two municipalities will participate in the study reaching about 1400 families per school year. In stakeholder workshops, key implementation determinants were identified according to the domains of the Consolidated Framework for Implementation Research. Through a consensus process with stakeholders, two bundles of implementation strategies were tailored to address context-specific determinants. Schools randomly assigned to group 1 will receive bundle 1 (Basic) and group 2 will receive bundle 1 + 2 (Enhanced). Bundle 2 consists of external facilitation, fidelity monitoring and feedback strategies. Secondary outcomes will include change in acceptability, appropriateness, feasibility, and organisational readiness as perceived by school staff. In addition, child weight status and diet, and parents’ feeding practices and risk of type 2 diabetes will be monitored. Linear and ordinal regression analysis will be used to test the effect on the primary and secondary outcomes, taking clustering and covariates into consideration where needed. Process evaluation will be conducted through key stakeholder interviews to investigate experiences of the program and perceptions on sustainability.

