### Randomisation and blinding

Within each municipality, schools will be randomised 1:1 to group 1 (Basic: bundle 1) or group 2 (Enhanced: bundle 1 + 2) using a computer-generated assignment by an independent statistician after baseline measurement has been conducted in September 2021. It is not possible to blind school staff and the research team to allocation, but parents and children will not get this information. The CONSORT flow diagram with the number of schools and children is shown in Fig. 2.

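### The stated power for the co-primary responsiveness score (0.29, 0.81, 0.99 at SD 8) is that of 400 independent parents per group and makes no allowance for randomising 30 schools

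*Protocol article*

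**What the plan says.** The abstract describes the design: "Thirty schools in two municipalities will participate in the study reaching about 1400 families per school year". Under Randomisation and blinding, the unit of allocation is the school: "Within each municipality, schools will be randomised 1:1 to group 1".

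Under Sample size and power calculation, the adherence power "was calculated for the sample size of 400 consenting parents in each group", by simulation. The responsiveness power "was calculated for the same sample size as above", for mean differences of 0.8, 1.6 and 3.2. On variability the section says: "The standard deviation was assumed to be 4, 8 and 16 for each option". It then gives the result for one of the three SDs: "With an SD of 8, the power for the three scenarios is 0.29, 0.81 and 0.99 respectively for this outcome".

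The section states no ICC, design effect, number of schools, parents per school or significance level. Elsewhere, the statistical analysis section plans mixed linear regression for the responsiveness score, and the abstract says that clustering will be taken into consideration where needed.

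**The concern.** The bundles are allocated to whole schools, and they act on principals, nurses and teachers. Parents in one school rate the same nurse's counselling and homework set by the same few teachers (Table 4), so some correlation within schools is to be expected. The protocol plans a mixed model for this score, yet its power figure appears to treat every parent as an independent observation. The planned analysis and the stated power would then rest on different variances.

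Responsiveness is one of two primary outcomes. A reader who takes 0.81 at face value would give a null result more weight than the design supports under those inputs.

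**Working it through.** **Inputs from the protocol.** 400 parents per group; differences 0.8, 1.6 and 3.2; SD 8; 30 schools randomised 1:1, so about 15 per arm; score range 4 to 20.

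**Assumptions.** Two-sided alpha 0.05; ICC from 0.01 to 0.10; equal school sizes; 400 per group read as the total over 15 schools. The protocol states none of these.

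**Step 1: reproduce the stated figures without clustering.** The standard error of the difference is 8 × √(2/400) = 0.566. The noncentrality is the difference divided by 0.566, referred to a t distribution with 798 degrees of freedom.

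| Difference | Noncentrality | Power | Stated |
|---|---|---|---|
| 0.8 | 1.414 | 0.292 | 0.29 |
| 1.6 | 2.828 | 0.806 | 0.81 |
| 3.2 | 5.657 | 0.9999 | 0.99 |

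The first two agree to two decimals. The third would round to 1.00 and seems to have been truncated. Other alphas do not fit: in the normal approximation, one-sided 0.05 gives 0.41 and 0.88 for the first two differences, and two-sided 0.025 gives 0.20 and 0.72.

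**Step 2: is there room for a hidden design effect?** Parents per school: 800/30 = 26.7. At an ICC of only 0.002 the design effect is 1 + 25.7 × 0.002 = 1.05, and the power for 1.6 is already 0.787, keeping 798 degrees of freedom. At ICC 0 with 28 between-school degrees of freedom (30 − 2) it is 0.78. The stated 0.81 contains neither adjustment.

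**Step 3: power for 1.6 at SD 8 with schools randomised.** Design effect (DE) = 1 + (26.7 − 1) × ICC; effective n per arm = 400/DE; standard error = 8 × √(2 × DE/400); t on 28 degrees of freedom.

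| ICC (assumed) | DE | Effective n per arm | Standard error | Power |
|---|---|---|---|---|
| 0.01 | 1.26 | 318 | 0.634 | 0.68 |
| 0.03 | 1.77 | 226 | 0.753 | 0.54 |
| 0.05 | 2.28 | 175 | 0.855 | 0.44 |
| 0.10 | 3.57 | 112 | 1.068 | 0.30 |

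Recruiting more parents per school has a ceiling. Effective n per arm cannot exceed 15/ICC, which is 300 at ICC 0.05, whereas power 0.81 at these inputs needs about 403 independent parents per arm.

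**Step 4: how far this depends on the SD.** The largest SD possible on a 4–20 score is half the range, (20 − 4)/2 = 8, reached only if half the parents score 4 and half score 20. An SD of 16 cannot occur. At SD 4, with the method of Step 3, the power for 1.6 is 0.98 at ICC 0.03, 0.95 at ICC 0.05 and 0.82 at ICC 0.10. At SD 8, a difference of 3.2 keeps 0.95 at ICC 0.05 and 0.82 at ICC 0.10.

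**The case against.** The strongest reply is that the loss is shown only at SD 8, the extreme of the scale. At the protocol's own SD 4, the clustered power for a difference of 1.6 stays at or above 0.82 over the whole assumed ICC range. That stands. A reader might infer from Step 3 that the trial is underpowered for responsiveness; the documents do not support that, because they fix neither the SD nor the ICC.

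A reader might also carry the design effect over to the adherence powers (0.44, 0.66, 0.86). That is not supported either. The inputs to that simulation are not given, and its results are lower than independent parents with evenly spread categories would give (about 0.67, 0.89 and 0.98 by the Whitehead formula). The simulation may already include clustering, or it may assume a skewed distribution; the protocol does not say.

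The figure of 26.7 parents per school rests on one reading of 400 per group. With two cohorts and about 1400 families per school year, the 400 could be per cohort or pooled.

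The planned analysis is not at fault, since a mixed model is specified, and the number of schools was set by availability (38 invited, eight declined). But neither the mixed model nor a later statistical analysis plan makes the printed 0.81 correct for 30 randomised schools. This is a stated figure that is wrong, not a detail left for later.

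**Conclusion.** The point holds for the stated responsiveness powers. They are the powers of an individually randomised comparison, and the reproduction in Step 1 shows this without needing any ICC. The size of the error does depend on the ICC: at the protocol's inputs of 1.6 and SD 8, the true figure lies between 0.68 and 0.30 for ICCs of 0.01 to 0.10, given equal school sizes, 26.7 parents per school and two-sided 0.05. Unequal school sizes or incomplete responsiveness items would lower it further.

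The conclusion is limited to that statement. It does not cover adherence, and it says nothing against the planned model.

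**What to change.** Restate the responsiveness power for 15 schools per arm, giving the ICC range, the number of parents per school, the between-school degrees of freedom, the significance level and an SD that is feasible on a 4–20 score. Remove SD 16. Report the minimum detectable difference over the same range.

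State whether 400 per group is per cohort or pooled over both cohorts. State whether the adherence simulation generated school effects, and rerun it if it did not.

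The cost is a short recalculation and one rewritten paragraph. No extra recruitment or change of design is needed. At any given difference and SD, the stated power will be less favourable.

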### Ethical approval

This study was approved by the Swedish Ethical Review Authority (protocol number Dnr 2021–02267) on July 7, 2021. Written informed consent will be obtained from all participants in the study such as school and primary care staff and parents. Parents will be answering questionnaires, participating in recorded MI-sessions, and give permission to use routine data of their child’s height and weight.

## Discussion

Many health promotion and prevention studies have been carried out in the school context around the world aiming to improve children’s dietary habits and increase physical activity and many lessons have been learned. The HSS parental support program builds on the growing evidence base of school-based health promotion programs. Thus far, HSS has been evaluated in three cluster-randomized trials during the past 10 years in Sweden including approximately 38 schools and 1000 families (33, 34, manuscript submitted). As a universal prevention program, the HSS reaches all children and parents across the socioeconomic and multicultural spectrum. The program is fully integrated into school routines and is moderately effective in improving dietary habits and physical activity in children and in one trial BMI in children with obesity was also reduced [34]. Process evaluations have consistently shown that the program is well received among teachers, parents, children and school nurses [16, 38–40, 52]. For these reasons, the HSS program is well-positioned for implementation research that aims to develop and test strategies that facilitate its uptake and use as part of routine practice in the school setting.

The lack of evidence regarding the effect of strategies to improve implementation in the school context has been pointed out as well as the need for robust measures of implementation outcomes [69]. In the Swedish context, IMPROVE is the first study to investigate the scaling up of an evidence-based family support program in primary school. It builds on well-established frameworks and models in implementation research such as CFIR [20] and Proctor’s outcome model [46]. IMPROVE is grounded in sound implementation methods as it emphasizes a systematic approach involving first the identification of context-specific determinants in tandem with stakeholders, and then tailoring strategies to tackle the identified determinants in an effective way. Using the SISTER taxonomy [26], this research will facilitate comparisons with other implementation studies in schools, both past and present. Finally, the use of a hybrid type 3 design is advantageous when there is a high momentum and mandate for implementation and the effects of the intervention are suspected to be vulnerable to a “voltage drop” when scaling up [45].

One barrier that is specifically addressed in IMPROVE is the engagement of parents. Low parental engagement has repeatedly been shown to be a challenge in previous evaluations of the HSS [39] and in other similar programs [70]. In this study we aim to make additional efforts to engage parents by producing an attractive 5-min film explaining the purpose and content of the HSS to be watched at the first meeting in school. Also, by gaining approval of implementation of the program at the municipality level through a memorandum of understanding, school principals will be given a more prominent role as advocates of the program towards both school personnel and parents. We have also added an implementation strategy to improve the school environment, culture and climate around health, which in previous studies of the HSS has received criticisms from parents in some schools for not being health-promoting [39]. The Enhanced strategy bundle consists mainly of monitoring and coaching by the research team. There is good evidence that external facilitation will lead to higher fidelity to the intervention components [53]. The T2D component was added in a previous trial of the program to increase parent’s interest and involvement, but was unfortunately not successfully implemented. There is an ongoing discussion about the boundary between parents’ and schools’ responsibility when it comes to healthy eating and sufficient physical activity of school children [43]. The Swedish guideline for school health care does encourage schools to support parents however it does not specify how to do this [30]. Thus, the IMPROVE study can contribute to knowledge on how to increase engagement in health promotion from both parents and school personnel. From the start of developing this program the aim has been to *begin with the end in mind*, meaning that the program should be integrated into existing school routines and be scalable. This was achieved in the third wave of the program, where trained school nurses performed the MI components, as also in IMPROVE. The program is now fully compatible with school routines and in line with existing guidelines such as the curriculum, the guideline for school health care and national guidelines on the prevention of unhealthy behaviours recommending family support regarding children 6–12 years of age.

Key success strategies when scaling up school-based interventions have previously been identified by Milat et al. [71]. These are the importance of systematic use of evidence, establishing monitoring and evaluation systems, calculation of cost, active engagement of the target community through a participatory approach, tailoring to the local context, infrastructure to support implementation, strong leadership and champions, political will, well defined scale-up strategy, and strong advocacy [71]. We believe that the IMPROVE study has the potential to address most or all these key factors to successfully scale up the HSS program.

Fidelity is critical to understanding whether the failure of an intervention on client outcomes is attributable to inadequate implementation or intervention failure, or some combination thereof. In the IMPROVE study, we have developed a comprehensive measure of fidelity that will allow the exploration of the effect of implementation strategies on single intervention components and different dimensions of fidelity. Fidelity to both intervention components and implementation strategies will be measured as recommended by Slaughter [27].

What are the chances that IMPROVE will lead to the sustainment of the HSS program? Previous studies have shown that important factors for successful implementation are that the intervention has a relative advantage over other programs, that there is a tension for change, an established need in the target group, and available resources [21]. Relative advantage should be secured by the fact that no other evidence-based program in this area is available today in schools in Sweden. Tension for change among stakeholders has existed for many years given that childhood obesity and social inequalities are on the rise. The prevalence of overweight and obesity among 8–9-year-old children is around 22% and considerably higher in areas with low socioeconomic status in Sweden as elsewhere [72]. In addition, there is a higher prevalence and earlier onset of T2D in adults with low socioeconomic status [73]. However, the question still remains whether the organisation, in this case, schools and primary care, are willing to collaborate in this endeavour, which will be tested in IMPROVE. If successful, the generalisability of this universal program is believed to be high, as it has been conducted in a great number of schools already in areas with low and mixed socioeconomic status, including families from different cultural backgrounds. The intervention components are flexible and can to a large extent be adapted to family needs.

### Limitations

There is no standardised operationalisation and methodology for measuring fidelity in school-based interventions [74], which are often multi-component and multi-level interventions. In our previous studies of the HSS program, we considered MI performance and quality as a measure of fidelity, whilst observing the number of classroom sessions being performed. In IMPROVE, we have constructed a much more comprehensive fidelity measure. This measure includes 13 specific indicators covering the fidelity dimensions: adherence, dose, quality of delivery, and participant responsiveness to the four components, as well as two measures combining the four components. This will give us an opportunity to test the effect of the strategies on various aspects of fidelity to individual components and combinations thereof. However, these indicators need further validation which will be addressed during the study by e.g. observation of classroom lectures. Another limitation is that causal mechanisms on how implementation strategies work will not be studied as this was considered to be too demanding for school personnel. This could be the topic of future studies.

### WHO trial registration data set

**Table Taba:** 

Data category	Information
Primary registry and trial identifying number	ClinicalTrials.gov ID: NCT04984421
Date of registration in primary registry	July 30, 2021
Secondary identifying numbers	None
Source(s) of monetary or material support	Swedish Research Council for Health and Working Life and Welfare (FORTE)
Primary sponsor	Swedish Research Council for Health and Working Life and Welfare (FORTE)
Secondary sponsor(s)	NA
Contact for public queries	MSc, PhD [contact]
Contact for scientific queries	MSc, PhD, [name], Karolinska Institutet, Stockholm, Sweden
Public title	IMPROVE
Scientific title	IMplementation and evaluation of the school-based family support PRogram A Healthy School Start to promote child health and prevent OVErweight and obesity (IMPROVE) – study protocol for a cluster-randomized trial
Country of recruitment	Sweden
Health condition(s) or problem(s) studied	Unhealthy diet, low physical activity, overweight and obesity, type 2 diabetes
Implementation intervention	All schools receive the Heathy School Start intervention. Active: Implementation strategy bundle 1 + 2 (Enhanced) Comparator: Implementation strategy bundle 1 (Basic)
Key inclusion and exclusion criteria	Inclusion: Public schools in two municipalities in the Stockholm Region. All children in pre-school class 5–7 years in these schools Exclusion: None
Study type	Parallel group cluster randomised trial
Date of first enrolment of schools	August 2021
Recruitment status	Not started
Primary outcome(s)	Fidelity to intervention (adherence and responsiveness)
Key secondary outcomes	Acceptability, appropriateness, feasibility, organizational readiness, fidelity to implementation strategies, child diet, child BMI, child weight status, parent’s risk of T2D, parental feeding practices

## Data Availability

Intervention materials (mostly in Swedish) are available from the project website www.ki.se/gph/enfriskskolstart. No data is yet available.

## Abbreviations

BMI: Body mass index
CFIR: Consolidated framework of implementation research
CFPQ: Comprehensive feeding practices questionnaire
EPAQ: Eating and physical activity questionnaire
ERIC: Expert recommendations for implementing change
HSS: The Healthy School Start program
LRIT: Leader readiness to implement tool
MI: Motivational interviewing
MINT: Motivational interviewing network of trainers
REDCap: Research electronic data capture
SRIT: Staff readiness to implement tool
T2D: Type 2 diabetes
